## **4.4. Unscheduled Visits**

During the study, the investigator may arrange unscheduled visits based on the actual situation of each subject. Clinically significant results from procedures, examinations and assessments at unscheduled visits should be recorded in the clinical medical records and CRFs. If clinically significant abnormalities are identified, the investigator will determine whether the subject needs to undergo reexamination, treatment, or hospitalization observation and the subject will be followed up until recovery or stabilized outcome.

## **4.5. Study Termination Criteria**

Study termination refers to the premature discontinuation of all study-related procedures during the clinical trial, with the primary objective of protecting the rights and interests of subjects and avoiding unnecessary harm.

Study termination will be considered if one of the following is met:

- If serious safety issues occur during the study, the study should be terminated in a timely manner;
- Major errors in the study protocol are found during the study, or important deviations occur in the implementation, which make the study endpoints difficult to evaluate;
- Termination requested by the sponsor (e.g., for reasons of funding and management);

- Study termination required by administrative authorities or the ECs;
- Other reasons.

Both the investigator and the sponsor have the right to terminate the study at any time. If it is necessary to terminate, it shall be implemented after consultation and consensus are reached between the two parties. In terminating the study, the sponsor and the investigator will assure that the interests of the subjects are adequately protected.

#### **4.6. Pregnancy/Lactation and Contraceptive Requirements**

A blood pregnancy test will be performed at screening and at EOS for female subjects of childbearing potential. During the study, a pregnancy test will be performed at the time specified in the procedure, and a blood or urine pregnancy test will be performed at the discretion of the investigator.

Female subjects and their partners must agree to use highly effective contraception methods (see Appendix 6) from the time of signing the ICF until 4 months after the last dose of IMP, and male subjects and their partners must agree to use highly effective contraception methods from the time of signing the ICF until 6 months after the last dose of IMP.

Women who have a positive blood pregnancy test at screening are not eligible for enrollment. If a female subject becomes pregnant while receiving the IMP, she will be withdrawn from the study immediately. If a female subject or the partner of a male subject becomes pregnant, the investigator should report it to the sponsor immediately. The investigator should obtain the result of pregnancy and report the condition of the fetus or newborn child to the sponsor.

## **5. Methods of Assessment**

### **5.1. Routine Assessments**

Demographic data: The subjects' age, sex, ethnicity, smoking history, alcohol consumption history and menstrual history will be inquired and recorded at screening.

Medical, surgical and medication history: ① History of SLE: The date of SLE diagnosis will be recorded. ② SLE medication history: The medication use (including specific drugs/treatment, dosage, and usage, etc.) for at least 2 years prior to the screening visit should be recorded. ③ Medical history of other diseases: The occurrence of other diseases (including disease name and time of onset, etc.) within at least 6 months prior to the screening visit should be recorded. ④ Previous treatment history of other diseases: The treatment (including specific drugs/treatment, usage and dosage, etc.) within at least 1 month prior to the screening visit should be recorded. ⑤ Previous surgical history: The surgery (including name and date of surgery, etc.) within at least 6 months prior to the screening visit should be recorded.

Body height, weight, BMI: Body height (cm) and weight (kg) will be measured during the screening period V1 (D-28 to D-1), and BMI will be calculated based on body height and weight. Only weight will be measured at visits V2, V6, V7, V8, V9, EOT, V12, and EOS.

Infectious disease screening: This will be conducted during the screening period V1 (D-28 to D-1) and includes: hepatitis B screening: hepatitis B five items (HBsAg, HBeAg, HBsAb, HBcAb, HBeAb, and HBV-DNA if necessary); hepatitis C screening: HCV antibody (HCV-RNA if necessary); HIV screening: HIV antibody; tuberculosis screening: chest X-ray (posteroanterior and lateral position), additional tuberculosis screening-related tests may be added according to the study site's diagnostic and treatment routine; syphilis screening: syphilis spirochete antibody.

### **5.2. Safety Assessments**

All samples will be collected by authorized study personnel. During the study, the site will review the test results based on the latest reference ranges (including laboratory tests and non-laboratory tests such as physical examination, vital signs, 12-lead ECG, etc.) and identify results outside the normal range. The investigator should assess whether the abnormal results obtained are clinically significant.

### **5.2.1. Physical Examination**

Physical examination includes head and face, eyes, ears, nose and throat, oral cavity, skin, lymph nodes, respiratory system, cardiovascular system, abdomen, genitourinary system (if necessary), musculoskeletal system, nervous system, and mental status. It will be conducted at V1 (screening visit), V2 (baseline visit), V3, V4, V5, V6, V7, V8, V9, V10 (EOT visit), V11, V12, V13, and V14 (EOS visit).

Unscheduled physical examinations may be performed as deemed necessary by the investigator. Abnormalities of physical examination judged by the investigator to be clinically significant should be recorded as AEs.

### **5.2.2. Vital Signs**

Vital signs include temperature, pulse, respiration, blood pressure. They should be measured at V1 (screening visit), V2 (baseline visit), V3, V4, V5, V6, V7, V8, V9, V10 (EOT visit), V11, V12, V13, and V14 (EOS visit).

Subjects should rest for at least 5 min before vital signs are measured. Pulse and blood pressure should be measured with the same arm whenever possible throughout the study.

In the event of abnormal blood pressure measurements, triplicate measurements (at least 5 min apart between two measurements) should be averaged. Additional measurement of vital signs may be performed as deemed necessary by the investigator. Abnormal vital sign findings judged by the investigator to be clinically significant should be recorded as AEs.

### **5.2.3. 12-lead ECG**

12-lead ECG includes heart rate, PR interval, QRS duration, QT interval, and QTcF [ $QTcF = QT/(RR^{0.33})$ ]. It will be conducted at V1 (screening visit), V2 (baseline visit), V3, V4, V5, V6, V7, V8, V9, V10 (EOT visit), V11, V12, V13, and V14 (EOS visit).

If blood samples need to be collected on the day of 12-lead ECG, the 12-lead ECG should be performed before blood collection or at least 20 minutes after the completion of blood collection. Subjects should rest for at least 5 min prior to examination.

Additional 12-lead ECGs may be performed as deemed necessary by the investigator. Abnormal 12-lead ECG findings judged by the investigator to be clinically significant should be recorded as AEs.

#### **5.2.4. Laboratory Tests**

Laboratory tests include hematology, blood chemistry, urinalysis, and coagulation function. See Section 3.9.1 for specific details. It will be conducted at V1 (screening visit), V2 (baseline visit), V3, V4, V5, V6, V7, V8, V9, V10 (EOT visit), V11, V12, V13, and V14 (EOS visit).

During the course of the study, the frequency of clinical laboratory tests may be increased if the investigator deems that it is necessary for safety considerations. Abnormal laboratory results judged by the investigator to be clinically significant should be reported as AEs.

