20. CRP and ESR results within 3 days prior to the first dose will be acceptable. Baseline examinations can be completed on D1 or within 48 hours before D1.
21. SLE flare assessment: The number of SLE flares, the severity of each flare, and the specific date of each flare need to be recorded. The severity of the flare refers to the SLE Flare Scoring Index (see Appendix 3).
22. Safety laboratory tests before the first dose, including pregnancy tests, can be completed on D1 or within 48 hours before D1.
23. Laboratory test results from the screening period can be used for the eligibility verification based on inclusion/exclusion criteria.

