| First dose                   | Within 2 hours before the start of infusion, 3 hours ( $\pm 15$ min) after the start of infusion, at the end of infusion (within 5 min), and at 2 hours ( $\pm 15$ min), 5 hours ( $\pm 30$ min), 24 hours ( $\pm 2$ h), 72 hours ( $\pm 4$ h), 168 hours ( $\pm 24$ h), 336 hours ( $\pm 24$ h), 504 hours ( $\pm 72$ h) after the end of infusion                                                         | Within 2 hours before the start of infusion, and at 24 hours ( $\pm 2$ hours), 168 hours ( $\pm 24$ hours), 336 hours ( $\pm 24$ hours), and 504 hours ( $\pm 72$ hours) after the end of infusion | Within 2 hours before the start of infusion and at 168 hours ( $\pm 24$ hours) after the end of infusion                          | Within 2 hours before the start of infusion                                                                                       |
| Second dose                  | Within 2 hours before the start of infusion                                                                                                                                                                                                                                                                                                                                                                 | Within 2 hours before the start of infusion and at 24 hours ( $\pm 2$ hours) after the end of infusion                                                                                             | Within 2 hours before the start of infusion                                                                                       | Within 2 hours before the start of infusion                                                                                       |

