In terms of safety, no DLTs have been observed to date. Treatment-emergent adverse events (TEAEs) occurred in 9/10 subjects, and treatment-related adverse reactions (TRAEs, i.e., IMP-related AEs) occurred in 7/10 subjects. However, the vast majority of TEAEs and all TRAEs were grade 1 or 2. The most common (incidence  $\geq 2/10$ ) TEAEs were infusion-related reactions (IRRs) (5/10), upper respiratory tract infection (3/10), hypokalemia (2/10), hyponatremia (2/10), hypertriglyceridemia (2/10), and back pain (2/10). The TRAEs experienced by the subjects were: IRR (5/10), aspartate aminotransferase (AST) increased (1/10), lymphopenia (1/10), hypertriglyceridemia (1/10), peripheral neuropathy (1/10), and rash (1/10). A total of 9 grade 3 TEAEs (no grade 4 or higher TEAEs) occurred in 4/10 subjects, all of which were unrelated to CM313 treatment.

In terms of efficacy, in the accelerated dose escalation low-dose levels (0.06, 0.3, and 1 mg/kg), all 3 subjects discontinued treatment due to disease progression. Additionally, 1 subject in the lowest dose level (0.006 mg/kg) withdrew voluntarily, with a neoplasm assessment finding of stable disease (SD). The best efficacy assessment findings for the 3 subjects in the 2 mg/kg dose level were very good partial response (VGPR), minor response (MR), and SD, respectively. For the 2 subjects in the 4 mg/kg dose level who had completed the first efficacy assessment, the neoplasm assessment findings were SD and VGPR, respectively. Currently, only 6 subjects in the 2 mg/kg and 4 mg/kg dose levels remain on CM313 study treatment.

Regarding PK, as shown in the table below, the mean PK parameters in 3 subjects in the 2 mg/kg dose level and 2 subjects in the 4 mg/kg dose level were similar to the mean PK parameters of daratumumab at the same dose. The clearance rate showed a decreasing trend with increasing dose and number of administrations, while the half-life showed an increasing trend with increasing dose and number of administrations, both exhibiting non-linear PK characteristics, suggesting target-mediated clearance of CM313.

| Parameter | CM313 dose level |
|-----------|------------------|
|-----------|------------------|

|                                        | 2 mg/kg             | 4 mg/kg           |
|----------------------------------------|---------------------|-------------------|
| Cmax (µg/mL)         |                     |                   |

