| 1st Dose             | 42.397±2.910        | 82.225±13.272     |
| 8th Dose             | 88.543±27.318       | NA                |
| AUC(0-inf) (µg·h/mL) |                     |                   |
| 1st Dose             | 1525.950±277.876    | 8688.199±4024.305 |
| 8th Dose             | 22445.339±15987.230 | NA                |
| T1/2 (h)             |                     |                   |
| 1st Dose             | 22.5±1.0            | 88.2±40.6         |
| 8th Dose             | 168.6±76.9          | NA                |
| CL (mL/h/kg)                    |                     |                   |
| 1st Dose             | 1.338±0.229         | 0.516±0.239       |
| 8th Dose             | 0.216±0.101         | NA                |
| V (mL/kg)                       |                     |                   |
| 1st Dose             | 43.224±5.832        | 58.631±0.162      |
| 8th Dose             | 47.450±1.801        | NA                |

In terms of PD, a decrease in the number of target cells (T/B/NK) from baseline was observed in 3 subjects in the 2 mg/kg dose level and 2 subjects in the 4 mg/kg dose level after the first dose. After multiple doses (QW\*7 times), the number of T cells could recover to baseline or even above baseline levels, while NK cells remained at a lower level. The PD characteristics were similar to the clinical study findings of daratumumab.

In summary, the current data indicate that CM313 has good safety and tolerability in patients with relapsed/refractory MM. The PK and PD characteristics are similar to those of daratumumab, and preliminary efficacy has been observed in the 2 mg/kg and 4 mg/kg dose levels.

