To date, there are no confirmed important risks for CM313. Based on the safety information of similar products already on the market, IRR, neutropenia/thrombocytopenia, interference with indirect antiglobulin test (IAT), and hepatitis B virus reactivation are listed as potential important risks of CM313.

As of 11 Jan 2022, the clinical trial data of CM313MM001 are as follows: 1) Safety: No DLT events have occurred so far. TEAEs occurred in 9/10 subjects and TRAEs occurred in 7/10 subjects, but the vast majority of TEAEs and all TRAEs were Grade 1 or 2. All Grade 3 TEAEs were judged to be unrelated to the IMP; 2) Efficacy: The best efficacy evaluation results of the

3 subjects in the 2 mg/kg dose level were VGPR, MR, and SD, respectively; while the neoplasm evaluation results of the 2 subjects in the 4 mg/kg dose level who had completed the first efficacy evaluation were SD and VGPR, respectively. The above findings indicate that CM313 has good safety and tolerability in patients with relapsed/refractory MM and lymphoma, and has shown preliminary efficacy.

Based on the mechanism of action of CM313, pharmacology findings, and preliminary efficacy findings, CM313 is expected to have potential benefits for the treatment of active SLE. Based on the available safety findings of CM313 and the safety data of the marketed product with the same target, daratumumab injection, CM313 has good safety and tolerability. Therefore, it can be considered that the overall benefits of CM313 outweigh the risks.

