#### **4.1.2.2. V3 (D8±1d)**

- Vital signs: including temperature, pulse, respiration, and blood pressure;
- Physical examination: including head and face, eyes, ears, nose and throat, oral cavity, skin, lymph nodes, respiratory system, cardiovascular system, abdomen, genitourinary system (if necessary), musculoskeletal system, nervous system, and mental status;
- 12-lead ECG: including heart rate, PR interval, QRS duration, QT interval, and QTcF;
- Laboratory test: including hematology, blood chemistry, urinalysis and coagulation function;
- PK, PD, and immunogenicity blood sampling. Please refer to Table 2 for specific sampling time points;
- Collection of prednisone dosage;
- Recording of AEs;
- Recording of concomitant therapies;
- Recovery and issuance of subject diary cards.

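### No neutrophil or platelet count is scheduled between the pre-dose sample and D8±1 after the first infusion, so an early fall that recovers within 6 to 8 days can go unrecorded

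*Protocol*

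**What the plan says.** Section 5.2.4 lists the visits at which hematology and the other safety laboratory tests are done: "See Section 3.9.1 for specific details. It will be conducted at V1 (screening visit), V2 (baseline visit), V3, V4, V5", and so on through all remaining visits to the last one. A note to Table 1 places the V2 sample before dosing: "Safety laboratory tests before the first dose, including pregnancy tests, can be completed on D1 or within 48 hours before D1". The next sample is at V3 (D8±1), where Section 4.1.2.2 asks for "Laboratory test: including hematology, blood chemistry, urinalysis and coagulation function".

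Section 3.4 names the risks carried over from similar marketed products: "IRR, neutropenia/thrombocytopenia, interference with indirect antiglobulin test (IAT), and hepatitis B virus reactivation are listed as potential important risks of CM313".

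Table 2 requires further blood in the first week. PK samples after the first infusion include "24 hours ( $\pm 2$ h), 72 hours ( $\pm 4$ h"), and a sample for immune cell typing is taken at 24 h. No hematology is attached to either time. The typing panel in Section 3.9.3 covers T, B, pDC and NK cells, not neutrophils or platelets.

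Section 2 counts laboratory tests among the primary safety endpoints. Sections 3.1 and 3.8.6 make the single-dose phase (D1–D28) the basis for opening the next dose level. Section 5.2.4 also lets the investigator order more frequent laboratory tests for safety reasons.

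**The concern.** The schedule leaves the first week after first exposure without a planned count of the two cell types that the protocol itself flags. A symptomless early fall that has recovered by V3 enters neither the single-dose safety review nor the laboratory tables unless someone happened to test. Under Sections 5.2.4 and 6.3.1 a laboratory abnormality becomes an adverse event only after it has been measured and judged clinically significant, so an unmeasured value cannot count toward the interruption criteria either.

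Entry limits make this somewhat more relevant. Exclusion criterion 3 admits subjects with platelets down to 50 × 10^9/L and white cells down to 2.5 × 10^9/L, so some may start with little reserve. Section 1.2.1 also notes low CD38 expression on platelets.

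What is at stake is the completeness of primary safety data at each level, when venepunctures that could supply the counts are already planned.

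**Working it through.** **1. Length of the gap.** V2 is pre-dose on D1. V3 is D8±1, so D7 to D9. The first post-dose count therefore comes 6 to 8 days after dosing: 144 h at the earliest, 168 h nominally, 192 h at the latest (ignoring the hours of the infusion itself).

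**2. What is drawn inside the gap.** At 24 h after the first infusion: PK and immune cell typing. At 72 h: PK only. Neither yields a neutrophil or platelet count.

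**3. What the added draws would leave.** With counts at 24 h and 72 h, the longest unmeasured stretch before V3 becomes 144 − 72 = 72 h (3 days) to 192 − 72 = 120 h (5 days), in place of 6 to 8 days.

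**4. Later doses.** V6 to V9 counts fall on dosing days, and the visit lists do not fix their time relative to the infusion. V10 is 7 days after the last dose. Counts are therefore weekly through the multiple-dose phase. Table 2 again has PK draws at 24 h and 72 h after the last infusion, and a typing draw at 24 h after the second.

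**5. Drug exposure during the gap (illustrative).** Section 1.3.2 gives first-dose parameters from the myeloma study, based on "the mean PK parameters in 3 subjects in the 2 mg/kg dose level and 2 subjects in the 4 mg/kg dose level".

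- Reproducing the 2 mg/kg half-life: ln 2 × V / CL = 0.693 × 43.224 / 1.338 = 22.4 h, against 22.5 h stated. It agrees.
- The same check at 4 mg/kg: 0.693 × 58.631 / 0.516 = 78.8 h, against 88.2 h stated. The agreement is looser, as it may be when a ratio of means is compared with a mean from two subjects.
- Fraction remaining, taking a single exponential: 0.5^(t / half-life).

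| Case | 24 h | 72 h | 144 h (D7) | 168 h (D8) | 192 h (D9) |
|---|---|---|---|---|---|
| First 2 mg/kg dose, 22.5 h | 47.7% | 10.9% | 1.2% | 0.57% | 0.27% |
| First 4 mg/kg dose, 88.2 h | 82.8% | 56.8% | 32.3% | 26.7% | 22.1% |
| Eighth 2 mg/kg dose, 168.6 h | 90.6% | 74.4% | 55.3% | 50.1% | 45.4% |

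Taking the 4 mg/kg half-life one standard deviation either way (47.6 h and 128.8 h) gives 8.7% to 40.5% at 168 h. The protocol gives no half-life for 8 or 16 mg/kg.

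**6. Steroid timing.** Section 3.8.2.3 recommends methylprednisolone before each infusion and daily on the two days after it. The 24 h draw (D2) falls on a steroid day. The 72 h draw (D4) falls on the day after the last prophylactic dose.

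**The case against.** The strongest objection is that a harmful gap has not been shown. The antibody acts by killing cells, so a fall could outlast the drug, and a nadir at or after D8 would appear at D8, D15, D22 or D29. The problem needs a fall that both starts and resolves within 6 to 8 days, and nothing in the protocol describes one. This stands. A reader might infer from the 22.5 h half-life that any fall would be over by D8. That does not follow, because drug remaining is not count recovery. The figure also belongs to one dose and three myeloma subjects; at 4 mg/kg over a quarter of the drug is still present at D8.

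A reader might also take the reported fall in lymphoid cells, "a decrease in the number of target cells (T/B/NK) from baseline was observed in 3 subjects in the 2 mg/kg dose level", as evidence for neutrophils and platelets. It is not. Those are other cells, already followed by typing at 24 h. The treatment-related events listed for the ten myeloma subjects include lymphopenia in one and no neutropenia or thrombocytopenia. Section 3.4 calls the risk potential and states that no important risk is confirmed.

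Nor do the documents show that escalation would be misjudged. Interruption is considered for moderate or worse related events of one system organ class in at least half of a level (5 of 10 subjects), for an unacceptable pharmacological event, or for serious events of one class in more than one subject. A symptomless dip that resolves untreated would seldom reach those criteria.

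The investigator may order extra tests. That is a partial remedy: such tests are likely to follow symptoms, and they give no uniform data across subjects and dose levels.

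Finally, weekly counts are a coherent choice and contradict nothing else in the protocol. That is true, and it limits this point to an improvement.

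**Conclusion.** A minor but real gap in safety measurement. For 6 to 8 days after the first infusion no neutrophil or platelet count is scheduled, although the protocol names the risk, treats laboratory abnormalities as primary endpoint data, and bases escalation on this phase. An early fall that recovers in that time can go unrecorded unless an extra test is ordered; one that lasts to D8 will be seen.

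The reading of the schedule needs no assumption. How often a fall would be missed cannot be estimated, because the protocol gives no time course for these counts. The figures of 0.6% and about 27% remaining at D8 assume that myeloma pharmacokinetics carry over to SLE and that elimination is a single exponential; they show only that exposure in the gap varies with dose. The stronger inferences, that a fall will be missed at all dose levels or that a low level will look safer than it is when the next one opens, are not supported.

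**What to change.** Add a routine hematology sample to the 24 h and 72 h draws already in Table 2 after the first infusion, and optionally after the last. Table 1 has no D2 or D4 column, so enter it in Table 2 or as a note to the hematology row. List the values in the single-dose safety review, which stays blinded, and include them in the laboratory summaries of Section 8.3.8.3.

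Compare with placebo only at the final unblinded analysis, pooling placebo across dose levels: 2 per level gives 8 subjects, or 6 if the optional 16 mg/kg level is not opened. Two placebo subjects within a level are too few, and the escalation review is not meant to see the allocation.

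The cost is one small extra tube and one routine count at two planned venepunctures, so 2 × 40 = 80 counts after the first infusion and 80 more if the last is included. No visit is added. The drawback is that prophylactic steroid affects both values, so leukocyte and neutrophil changes need cautious reading.
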